### Subject adherence, withdrawal, safety measures and adverse events

Adherence will be measured at each visit. Subjects will be asked about their dietary intake and physical activity. Subjects in the ILI will be asked to return any empty packets or unused meal replacement products to examine usage. Subjects who are found to be non-adherent or withdraw in the first 6 weeks of the study will be replaced.

The subject has the right to withdraw their consent anytime without giving any reason. The subject’s reason for withdrawal (if reported) will be recorded. Subjects will be notified that if they choose to withdraw from the study, the investigative team will not proceed with further assessments and data collection but their previously collected data will be used for research purposes. Withdrawal from the study will be recorded in the electronic medical record.

Also, the study will withdraw the subject if:The subject is unable to adhere to the study protocol and study requirements;There is a significant protocol deviation;The subject becomes pregnant during the study;Any new illness that affects their inclusion (exclusion criteria above);Continuing in the study is deemed harmful to the subject’s health;The subject is lost to follow up;The trial cancels.

All female subjects will be asked to report if they miss any menstrual cycle. A urine pregnancy test will be conducted and subjects withdrawn if the test is positive.

Any harm that may result in a subject’s withdrawal, or is present at the end of the study, will be followed up until a satisfactory resolution occurs. Safety measures include home capillary blood glucose monitoring (for hyper- and hypoglycaemia), blood pressure measures, electrocardiogram at baseline (to identify any covert cardiac disease that may affect physical activity), and laboratory measures to assess any blood, liver, renal, or nutritional abnormalities. Specific advice will be given regarding home blood glucose monitoring for hypo- and hyper- glycaemia, as well as other foreseeable changes associated with weight loss or dietary change and increased activity. Medications that may increase risk of adverse effects will be discontinued.

All adverse events (AE) will be collected and reported using specific forms. At every visit, the subject will be asked about any experiences by asking: “since your last visit, have you experienced any problems?” All AEs will be recorded and evaluated by the Investigators.

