### Sample size calculations

The sample size is based on the number of subjects needed to provide a power equal to 0.8 to test the primary hypothesis at the 0.05 significance level. The primary outcome for the proposed study is weight loss at 12 months. We anticipate that the weight loss will be 7% higher in the lifestyle group compared to the usual care group at 12 months. The Look AHEAD study yields a conservative estimate of the standard deviation of percentage of weight loss across various populations to be 9%. Using ANCOVA method to calculate the sample size and with 30% inflation for dropouts, 69 subjects per group are needed for the primary outcome. Regarding glycaemic control, Unick et al. found a − 0.643 (± 0.99) % change [81]; however, a change of 0.5% is considered to be clinically significant and comparable to changes achieved with most diabetes medications. The 69 subjects per group is also sufficient to detect a 0.5% change in HbA1c (assuming SD = 1%; the same power, significant level, and dropout rate). The study will therefore aim to recruit a total of 138 subjects (69 per group) including a 30% dropout.

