### Subject replacement

Any subject who drops out or is withdrawn in the first 6 weeks of study participation will be replaced. We estimate about 10% of recruited participants will be in this category.

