The main objective of the proposed study is to examine the effectiveness of an ILI. The ILI will be compared to usual care. The study will examine the primary outcome of weight loss, and also focus on improvement in glycaemic control. This will be assessed using an ANCOVA model. The first response variable will be weight at one year. The covariates will be weight at baseline and a binary variable indicating whether the subject was in the intervention group or the usual group. The regression coefficient of the group term represents the effect size of the intervention. In addition to this unadjusted analysis, an adjusted analysis will also be performed by adding body fat, fat free mass, HbA1c, and medication as covariates in the model. Similar unadjusted and adjusted ANCOVA models to assess glycaemic control using HbA1c will be fit. The primary analyses will be done using the intention-to-treat (ITT) method. Secondary outcomes (body composition and weight loss maintenance, insulin sensitivity/resistance, cardiovascular health and risk, impact on diabetes complications and liver function, changes in physical activity, mood, and quality of life) will be analysed in the same way, using unadjusted and adjusted analyses, under the ITT principle. Continuous measures will be analysed using an ANCOVA model and categorical outcomes using the appropriate generalised linear model, with the baseline measure of the outcome as a covariate. All outcome measures will also be analysed with per protocol.

In case of missing values, data imputation as well as comparison between imputed and non-imputed scores will be undertaken. A macro will be written that, for each measure, 1) identifies each pattern of missing data that occurs for the items used to construct the measures, 2) performs a separate regression analysis for each pattern predicting the measure value, for those with complete data, from the non-missing items for that pattern, and 3) uses the regression equation to replace the missing measure value with the regression-based predicted score for people having that pattern of missing data. Missing data are only replaced with predicted scores when the regression analysis indicates that the predicted score is a good estimate (i.e., when R-squared > 75% for the regression equation; almost always the case except for those who are missing more than 50% of items). Subgroup analysis will be performed gender and baseline BMI (< 30 and > = 30 kg/m^2^).

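### Replacing randomised subjects for non-adherence or withdrawal in the first 6 weeks is likely to drop early diet failures from a 12-month comparison that the protocol calls intention-to-treat

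*Protocol article*

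**What the plan says.** The section on adherence, withdrawal and safety states the rule: "Subjects who are found to be non-adherent or withdraw in the first 6 weeks of the study will be replaced". The same section lets the study itself withdraw a subject who cannot keep to the protocol. It says that when a subject chooses to withdraw, assessments and data collection stop, while data already collected are kept.

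The Subject replacement section restates the rule for those who drop out or are withdrawn in the first 6 weeks, without naming non-adherence, and adds: "We estimate about 10% of recruited participants will be in this category".

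The Data analysis section says: "The primary analyses will be done using the intention-to-treat (ITT) method". Per-protocol analyses are additional.

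The Sample size section says: "The study will therefore aim to recruit a total of 138 subjects (69 per group) including a 30% dropout". It does not mention replacement. The Abstract describes the same 138 as the number for assessing the primary outcome.

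The randomisation section describes a concealed 1:1 list and says that a dropout's study number is not used again. No section says whether a replaced subject stays in the ITT set, or to which arm the new subject goes.

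**The concern.** Whether a subject is adherent in the first 6 weeks can be known only after allocation, and it depends on what the subject was allocated to. In the ILI arm those weeks fall within the 12-week phase at about 800 kcal a day. If subjects who cannot manage that phase are exchanged for others and then have no 12-month weight, the comparison estimates the effect in people who tolerate the start of the diet. It no longer estimates the effect of offering the programme. The trial describes itself as pragmatic and asks about effectiveness, so early intolerance is part of the answer it seeks.

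**Working it through.** **1. Is the rule applied equally in the two arms?** Its wording covers both. The opportunity to detect non-adherence differs:

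| | ILI | Usual care |
|---|---|---|
| Scheduled contact | Dietitian and trainer every 2 weeks (Table 3), so about three visits in 6 weeks | Clinic every 3 months, with monthly telephone or electronic contact in between |
| Objective check | Return of packets and unused product | None described |
| Task in the first 6 weeks | Meal replacement at about 800 kcal | Standard advice |

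On this schedule no routine usual-care clinic visit after baseline falls in the window.

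**2. Can ITT be carried out for replaced subjects?** Those who choose to withdraw have no later assessment, so they have no study weight at 12 months. No continued follow-up is stated for those whom the study withdraws. The only imputation method described predicts a multi-item score from its own non-missing items. Body weight has no items, so that method cannot supply the value.

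**3. The plan's own sample size.** Inputs from the Sample size section:
- "provide a power equal to 0.8 to test the primary hypothesis at the 0.05 significance level" (two-sided assumed)
- "We anticipate that the weight loss will be 7% higher in the lifestyle group compared to the usual care group at 12 months"
- "conservative estimate of the standard deviation of percentage of weight loss across various populations to be 9" (percent)
- 30% dropout

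n = 2(1.96 + 0.84)² × 9²/7² = 26 per group; 26/0.7 gives 38 per group, or 76 in total. The stated 69 is not reproduced. A baseline-outcome correlation would only lower the figure (with 0.5, assumed: 20, then 29). For HbA1c (0.5, SD 1) the same formula gives 63, then 90; with an assumed correlation of 0.5 it gives 48, then 69. For weight, therefore, 138 is more than the inputs require.

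**4. Power for weight.** Evaluable per group: 69 × 0.7 = 48. Standard error: 9 × √(2/48) = 1.84.
- Effect 7.0: Φ(7.0/1.84 − 1.96) = 96.8%.
- Effect 6.3: Φ(6.3/1.84 − 1.96) = 92.9%.

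**5. Illustrative dilution.** Assume that a share f of the ILI arm is removed, that those subjects gain nothing, and that the usual-care mean is unaffected. The effect in everyone randomised is then 7.0 × (1 − f):
- f = 5%: 6.65
- f = 10%: 6.3
- f = 20%: 5.6

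The protocol gives 10% overall and no figure by arm.

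**6. Illustrative bias with no true effect.** Assume SD 9, 48 per group, and a correlation r of 0.2 to 0.5 between the tendency to be removed and a poor outcome. Removing a fraction f shifts an arm's mean by 9 × r × φ(q)/(1 − f), where q is the (1 − f) normal quantile. The bias is the difference between the arms:

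| Removed, ILI v usual care | Bias (points) | Type I error |
|---|---|---|
| 10% v 10% | 0 | 5.0% |
| 15% v 5% | 0.30 to 0.75 | 5.3% to 6.9% |
| 20% v 0% | 0.63 to 1.57 | 6.4% to 13.7% |

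**7. Number randomised.** If 138 are to remain after 10% are replaced: 138/0.90 = 153.3, or 154 for equal arms. If the 10% is taken of 138: 138 × 1.10 = 152. That is 14 to 16 more than 138. If the 30% applies after replacement, 138 × 0.7 = 96.6 are evaluable, and the total loss is 1 − 96.6/152 = 36.4% to 1 − 96.6/154 = 37.3%.

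**The case against.** The strongest reply is that replacement and ITT can coexist. Nothing says that replaced subjects are deleted. Their earlier data are kept, their numbers are not reused, and per-protocol is only an additional analysis. That fits recruiting one more subject while keeping the original, and a fuller protocol or analysis plan may define the set. This stands against a reading that a reader might infer, namely that the plan flatly contradicts ITT. It does not answer the second step above: however the set is defined, subjects who choose to withdraw have no study weight at 12 months.

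The rule is also neutral in wording, usual-care subjects can leave early too, and equal removal gave no bias in the illustration. So a benefit to ILI is an inference from the visit schedules and not something the protocol documents.

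The two statements of the rule may differ less than they seem to. Subjects whom the study withdraws for non-adherence fall under both. Only subjects judged non-adherent but not withdrawn are treated differently.

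Finally, replacement is not the sole cause. A subject who withdraws lacks a 12-month weight whether or not someone is recruited in their place. This stands, and it is why the fix must cover follow-up as well as the replacement rule.

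**Conclusion.** The concern holds in a limited form. A rule that depends on behaviour after randomisation sits beside a primary ITT analysis. Early adherence is observed mainly in ILI, and data collection stops when a subject chooses to withdraw. Early diet failures are therefore likely to be missing from the 12-month comparison, possibly in favour of ILI. The size cannot be derived from the protocol. The fall from 7.0 to 6.3 assumes that 10% of the ILI arm is removed with no benefit, and the bias figures rest on an assumed split between arms and an assumed correlation.

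Two stronger readings are not supported. A reader might infer that 138 is the wrong total, but it is a recruitment target that more than covers the weight outcome. What needs settling is what 138 denotes, since it cannot be both the number randomised and the number left after replacement. A reader might also infer that early losses are counted twice, in the 30% and again through replacement. The protocol does not say whether the 10% lies inside the 30%, so overlap is possible but not shown.

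**What to change.** - Remove non-adherence as a ground for replacement, and reconcile the two sections that state the rule.
- State that every randomised subject stays in the ITT set in the assigned arm, including any already replaced, since the trial is under way.
- Separate stopping the intervention from stopping follow-up. Unless consent to data collection is withdrawn, seek a 12-month weight by visit or, with permission, from the medical record. The protocol already asks permission to use those records and plans to take body weight from them after the study.
- Randomise any additional subject as the next number on the list, not into the arm of the person who left.
- Report the true number randomised, about 152 to 154 if 138 are to remain after 10% replacement. Say whether the 10% is part of the 30%, and reconcile what 138 denotes in the Abstract and the Sample size section.

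The cost is protocol wording, some effort to trace weights, a few subjects with sparse data in the analysis, and a possibly smaller estimate. Power for weight remains above 90% at an effect of 6.3 with 48 evaluable per group.

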### Case report forms and data entry

Subjects will be asked for permission to obtain their clinical information from their electronic medical records. Paper case report forms (CRFs) will be completed for each visit. Each CRF will be validated by a research investigator. The CRF data will be translated into electronic data. All data will be double entered into a secure electronic database in preparation for data analysis.

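### Subjects withdrawn by the study for non-adherence or protocol deviation appear to lose the 12-month weight that the ITT primary analysis needs

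*Protocol article*

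**What the plan says.** The relevant text is in four sections of the protocol article.

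- *Subject adherence, withdrawal, safety measures and adverse events* tells subjects that, if they choose to withdraw, "the investigative team will not proceed with further assessments and data collection but their previously collected data will be used for research purposes". It then lists grounds on which the study itself withdraws a subject. Two of them are "The subject is unable to adhere to the study protocol and study requirements" and "There is a significant protocol deviation". The only follow-up after withdrawal that it mentions is for harm that leads to withdrawal or "is present at the end of the study, will be followed up until a satisfactory resolution occurs".
- The same section adds an early rule: "Subjects who are found to be non-adherent or withdraw in the first 6 weeks of the study will be replaced". *Subject replacement* repeats this for dropouts and withdrawals and sizes it: "We estimate about 10% of recruited participants will be in this category".
- *Data analysis* takes weight at one year as the response in an ANCOVA with baseline weight and group. It states: "The primary analyses will be done using the intention-to-treat (ITT) method". A per-protocol analysis is planned separately.
- *Case report forms and data entry* says: "Subjects will be asked for permission to obtain their clinical information from their electronic medical records". *Intervention duration and follow-up* names body weight from electronic records only under the post-study phase of the ILI schedule.

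**The concern.** An ITT analysis of weight at one year needs that weight from everyone randomised, whether or not they kept to the programme. The withdrawal list takes subjects out of the study because of behaviour after randomisation, and that behaviour is closely tied to the outcome: someone who cannot keep to a low-energy diet will usually lose less weight. If follow-up ends at that point, the data set labelled ITT drifts towards the per-protocol set, which the plan already analyses in its own right.

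The loss is unlikely to be even. The ILI arm is asked for about 800 kcal a day for 12 weeks, 150 minutes or more of weekly activity, and two-weekly dietitian and trainer sessions up to week 24. Returned packets are checked in that arm only. UMC has three-monthly clinics and monthly remote contact. Allocation is known to all. The primary estimate is therefore at risk of flattering ILI.

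**Working it through.** **Step 1: does the text lead to missing 12-month weights?** The stop on data collection is explicit for subjects who choose to withdraw. The list of study-initiated withdrawals follows directly, introduced as an addition to the same topic. No different data rule is given for these subjects, and only harms are said to be followed up. The natural reading is that their later weights are not collected. Weights already taken are kept.

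**Step 2: can the imputation rule fill the gap?** The rule in *Data analysis* predicts a measure from its own non-missing items and replaces it only if R-squared exceeds 75%. A body weight has no items. Even if baseline weight were used as the predictor, the equation is fitted in subjects with complete data, so a withdrawn subject would be predicted as if he or she had stayed.

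**Step 3: is this a matter of power?** No. The section *Sample size calculations* gives a 7-point difference, SD 9, power 0.8, alpha 0.05 (taken as two-sided), 30% dropout and 69 per group.
- Per group: n = 2(1.96 + 0.84)² × 9² / 7² ≈ 26, and 26/0.7 gives 38. The weight inputs therefore do not reproduce 69. The HbA1c inputs (0.5, SD 1) do so if a baseline correlation of 0.5 is assumed (48, and 48/0.7 gives 69), but the article states no correlation. This is a separate matter.
- Completers: 69 × 0.7 = 48.3, so 48 per group. 7 / (9 × √(2/48)) = 3.81, and 3.81 − 1.96 = 1.85, which is power of 96.8%.

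The trial can lose 30% and still detect the planned weight difference. The threat is bias.

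**Step 4: how large could the bias be?** Let *w* be the share of the ILI arm withdrawn in this way and *g* the shortfall in their weight loss against the rest of the arm, in percentage points. With *m* the difference from UMC among ILI subjects who stay:

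ITT difference = (1 − w)m + w(m − g) = m − wg, so m = ITT difference + wg.

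Take the ITT difference as the planned 7 points. The values of *w* and *g*, and the absence of such loss in UMC, are assumptions.

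| w | g = 3 | g = 5 | g = 7 |
|---|---|---|---|
| 10% | 7.3 | 7.5 | 7.7 |
| 20% | 7.6 | 8.0 | 8.4 |
| 30% | 7.9 | 8.5 | 9.1 |

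If UMC also loses non-adherers, the bias becomes w·g in ILI minus w·g in UMC, so equal losses of equal size would cancel.

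**The case against.** The strongest reply is that the decisive link is a reading. The sentence ending data collection covers subjects who choose to withdraw, and nothing states that it applies to those whom the study withdraws. The article condenses a fuller protocol that may settle this. That stands as a limit on how firmly the point can be put. It does not remove the point: the article gives one data rule after withdrawal, places the study-initiated grounds beside it, and claims ITT without reconciling the two.

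A reader might also infer four stronger things, none of which the documents support.
- *That outcome weights are thrown away by rule.* Earlier data are expressly kept; at most, later weights go uncollected.
- *That electronic records are closed to the trial before the post-study phase.* Record-based weight is named only there, but the permission sought has no such limit. The plan neither assigns records to withdrawn subjects nor excludes this.
- *That 30% of the ILI arm will be lost as non-adherers.* The 30% is overall dropout. It would also cover withdrawn consent, pregnancy, illness and loss to follow-up, and the Discussion notes a transient population. The share due to this rule is unknown, so 30% is an upper case.
- *That the bias must favour ILI.* The criteria apply to both arms, and uneven loss is inferred from uneven demands. The direction is likely, not certain.

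**Conclusion.** The point holds as a conflict between the withdrawal rules and the ITT primary analysis. On the natural reading, subjects withdrawn for non-adherence or protocol deviation have no weight at one year, for a reason related to that weight, and the stated imputation cannot replace it. The six-week replacement rule, which also turns on adherence, adds to the problem.

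The size cannot be derived from the documents. Under the assumptions in the table, a true 7-point difference would be estimated at about 7.3 to 9.1 points, an excess of 0.3 to 2.1. The low end needs only a tenth of the ILI arm to be affected. The high end treats a share as large as the whole planned dropout as withdrawn for this reason, with a 7-point shortfall. Both ends assume no matching loss in UMC.

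**What to change.** Reconcile *Subject adherence, withdrawal, safety measures and adverse events*, *Subject replacement* and *Data analysis* by separating withdrawal from the intervention from withdrawal from data collection.

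- Leave the clinical withdrawal criteria as they are.
- For subjects whom the study withdraws for non-adherence or protocol deviation and who have not withdrawn consent, keep seeking weight, HbA1c and medication at 12 and 24 months. Use the scheduled visits or, where the permission has been given, the electronic record.
- Include these subjects in the ITT analysis as randomised, including any for whom a replacement was recruited.

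The cost is a protocol and consent amendment through the three institutional review boards and the ministry named in *Ethical approvals and monitoring*, for a trial already under way. Subjects enrolled under the present wording may need to be asked again. There will be some visits for subjects off the programme, and the estimated effect may be smaller. Subjects who refuse further data collection or cannot be traced will still be missing, so the change reduces the bias without removing it. It is worth making early, because a 12-month weight not taken at the time may not be recoverable later.

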#### Intervention duration and follow-up

The intervention will be for 12 months for the primary outcome measure with 12 months further follow-up.

The 2 study arms will have the following schedule:i.Intensive Lifestyle Intervention Group:InterventionPHASE 1: 12 weeks LED + physical activity;PHASE 2: 12 weeks partial LED + physical activity;PHASE 3: 6 months own food, physical activity, and lifestyle change.Follow-upd.PHASE 4: 12 months follow-up;e.PHASE 5: Post-study follow-up via electronic medical records (including body weight, medications, and biochemical measures).ii.Usual Medical Care Group:There will be 12 months usual care (optimising individualised glycaemic, blood pressure, and lipid control) with standard diet and activity advice, and a further 12 months follow-up. Contact frequency will be based on the current recommended usual care 3-monthly clinic attendance. To maintain participation in the study, the subjects in this group will receive regular monthly contact during the intervention from the research team via telephone and electronically in between formal visits.

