#### Schedule of visits (ILI)

Table 3 shows the schedule of intervention visits for the ILI group.

**Table 3 Tab3:** Study phases and visit schedules for the intensive lifestyle intervention

Phase	Timeline	Individual Visit Schedule
1. Low Energy Diet + Physical Activity	Weeks 1–12	Visit every 2 weeks Dietitian (30 min/visit) Exercise trainer (30 min/visit)
		Physician review at baseline and on completion of Phase 1
2. Partial Low Energy Diet + Physical Activity	Weeks 13–24	Visit every 2 weeks Dietitian (30 min/visit) Exercise trainer (30 min/visit)
		Physician review on completion of Phase 2
3. Lifestyle change	Weeks 25–48	Visit every 4 weeks Dietitian (30 min/visit) Exercise trainer (30 min/visit)
		Physician review at 3-month and on completion of Phase 3
4. Follow-up	Weeks 49–96	3 monthly visits for follow-up Dietitian (30 min/visit) Exercise trainer (30 min/visit)
		Physician review at 3-month intervals and completion of Phase 4
5. Post Study	Minimum 2 years post-study	Review by weight management service Collection of data via electronic medical records

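### Adverse events are asked about at visits, and the lifestyle arm has 18 visits to usual care's 4 in the intervention year, so mild self-reported events are likely to look relatively more frequent under the lifestyle programme

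*Protocol article*

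**What the plan says.** Three parts of the protocol article bear on this.

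- **Elicitation.** The section on adherence, withdrawal, safety measures and adverse events says: "At every visit, the subject will be asked about any experiences by asking" an open question, "since your last visit, have you experienced any problems". Both the occasion and the reference period are thus defined by visits. The section on case report forms likewise has paper forms completed for each visit.
- **Lifestyle schedule.** Table 3, under Schedule of visits (ILI), sets "Visit every 2 weeks" for weeks 1–12 and again for weeks 13–24, then a visit every 4 weeks for weeks 25–48. In weeks 49–96 visits are 3-monthly.
- **Usual-care schedule.** Under Intervention duration and follow-up: "Contact frequency will be based on the current recommended usual care 3-monthly clinic attendance". For the sake of retention, "the subjects in this group will receive regular monthly contact during the intervention from the research team via telephone and electronically in between formal visits". These contacts are distinguished from formal visits, and nothing in the text attaches the adverse-event question or a form to them.

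The Secondary objectives section makes investigation of side effects and adverse outcomes of the intervention an aim of the study. The Study design section describes the trial as open-label.

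**The concern.** The two arms are asked the same question at very different frequencies over very different recall periods. The Background lists the common adverse events of low-energy diets, among them dizziness, fatigue, constipation, flatulence and dry skin. Many of these are mild and subjective, and such symptoms are sensitive to how often a person is prompted and how far back they must remember. Somebody asked after two weeks is more likely to mention a few days of dizziness than somebody asked after three months.

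The direction is predictable: with no true difference, more such events would be recorded under the lifestyle programme. At stake is any adverse-event table by arm, which a reader would naturally take as describing the tolerability of the programme relative to usual care. Later analysis cannot recover usual-care events that were never mentioned, so the remedy lies mainly in data collection.

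**Working it through.** The article states no number of enquiries and no adverse-event rate, so there is no figure to reproduce. The counts follow from the schedule.

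**Step 1: enquiries in the intervention year (phase length ÷ visit interval)**

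- Lifestyle, weeks 1–12: 12/2 = 6
- Lifestyle, weeks 13–24: 12/2 = 6
- Lifestyle, weeks 25–48: 24/4 = 6
- Lifestyle total: 6 + 6 + 6 = 18
- Usual care: 12 months/3 = 4
- Ratio: 18/4 = 4.5

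**Step 2: recall period per enquiry**

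- Lifestyle: 2 weeks, then 4 weeks (mean 48/18 = 2.7)
- Usual care: 48/4 = 12 weeks on the 48-week schedule, or 52/4 = 13 weeks on a calendar year

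**Step 3: what this could do to reported rates.** The document gives no recall rate, so this step rests on an assumption. Suppose the chance that an event is reported halves every *h* weeks after it happens, and events occur evenly over time at the same true rate in both arms. With λ = ln 2/*h*, the average reporting probability over an interval of *w* weeks is

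R(w) = (1 − e^(−λw))/(λw).

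The lifestyle arm spends 24 weeks on 2-week intervals and 24 on 4-week intervals, so its average is [24·R(2) + 24·R(4)]/48. Usual care is R(12).

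For *h* = 4: λ = 0.1733, R(2) = 0.845, R(4) = 0.721, lifestyle average 0.783, R(12) = 0.421, ratio 0.783/0.421 = 1.86.

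| Assumed half-life (weeks) | Lifestyle | Usual care | Spurious ratio | Ratio if monthly contacts also ask (usual care = R(4)) |
|---|---|---|---|---|
| 2 | 0.631 | 0.237 | 2.67 | 1.17 |
| 4 | 0.783 | 0.421 | 1.86 | 1.09 |
| 8 | 0.882 | 0.622 | 1.42 | 1.04 |
| 13 | 0.925 | 0.739 | 1.25 | 1.03 |
| 26 | 0.961 | 0.856 | 1.12 | 1.01 |
| 52 | 0.980 | 0.924 | 1.06 | 1.01 |

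Using 13 weeks for usual care changes little: at *h* = 4, R(13) = 0.397 and 0.783/0.397 = 1.97; at *h* = 26, R(13) = 0.845 and 0.961/0.845 = 1.14.

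**Step 4: effect of using the monthly contacts.** Monthly contact between 4 visits adds up to 12 − 4 = 8 occasions, so usual care would have about 12 enquiries and the ratio of enquiries falls from 4.5 to 18/12 = 1.5. Over half-lives of 4 to 26 weeks the spurious ratio falls from 1.86–1.12 to 1.09–1.01.

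**The case against.** The case against has several strands.

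- **No between-arm safety test is specified.** The secondary outcomes listed in the Data analysis section do not include adverse events, and the stated aim concerns side effects of the intervention. This stands as a limit: the point applies to whatever by-arm comparison is reported, and not to a planned test.
- **A common schedule may exist out of sight.** Figure 2, which covers assessments in both groups, is not shown, and the full protocol is not supplied. This also stands. The rule that is visible is nevertheless tied to visits, and confirming or correcting it is cheap.
- **The monthly contacts might already pick up events.** A reader might infer that they serve retention only. The text gives retention as their purpose but does not exclude adverse-event reporting, and it says that all adverse events are collected. What can be said is that no adverse-event question is stated for them.
- **No period is structurally missed.** The question covers the whole interval since the last visit in both arms. That is correct; the bias comes from longer recall and fewer prompts. A reader might infer a threefold inflation by supposing perfect recall for 4 weeks and none after (4/13 = 31% captured, ratio 3.2; with 8 weeks, 8/13 = 62%, ratio 1.6). The documents give no support for such a cut-off. With gradual forgetting, only a half-life near 2 weeks brings the ratio to 2.67.
- **Unequal contact is inherent in comparing an intensive programme with usual care.** True of the care itself, but the adverse-event enquiry need not follow the same pattern, since the research team is already in monthly contact with usual-care subjects.

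**Conclusion.** The concern holds in a limited form. Followed as written, the rule gives 18 enquiries with 2- to 4-week recall in the lifestyle arm and about 4 with roughly 13-week recall in usual care. Comparisons of mild, self-reported events in the intervention year are therefore likely to be inflated in the lifestyle arm. The counts come straight from the document. The size of the bias does not: about 1.9 to 1.1 as a ratio rests on an assumed recall half-life of 4 to 26 weeks, equal true rates and no enquiry at the monthly contacts.

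A reader might conclude that the safety data as a whole cannot be interpreted. The documents do not support that. Serious and laboratory-detected events depend far less on prompting; the same section also provides for laboratory measures, blood pressure and home glucose monitoring, and access to medical records is sought. The imbalance concerns the intervention year, because lifestyle visits become 3-monthly afterwards. Its direction is towards overstating harm from the programme relative to usual care.

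**What to change.** 1. Ask the same scripted question, on the same form, at the monthly usual-care contacts already planned, with the reference period reworded to the time since the last visit or contact. If Figure 2 or the full protocol already provides for this, say so in the adverse-event section.
2. Keep every lifestyle-arm event in the comparison. One way is to count subjects with at least one event in each common 4-week or 3-month window, in both arms.
3. Do not restrict the table to a monthly grid with events from the extra lifestyle visits listed apart. In weeks 1–24 each visit covers only 2 weeks, so one visit in every 4 weeks would retain 2/4 = half of the lifestyle arm's non-serious event time and under-count its events.
4. Report the number of enquiries made per arm beside the rates. The trial is under way, so this matters especially for data already collected, where the gap cannot be closed afterwards.

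The cost is one question and one form per existing contact, some data entry, and slightly higher usual-care event counts. A small imbalance remains in weeks 1–24 (2-week against about 4-week recall), worth roughly 1.01 to 1.09 under the same assumptions taken over the whole intervention year.
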